### Procedure for unblinding if needed {17b}

Unblinding will not be necessary in this trial.

## Data collection and management

### Plans for assessment and collection of outcomes {18a}

Primary and secondary outcome data along with sociodemographic characteristics and potential confounders will be collected electronically using tablets equipped with KoboCollect software. Data collection will occur at baseline, 3-month and 12-month post-intervention. Baseline and 12-month follow-up assessments will be conducted in person at a central location, while 3-month follow-up assessments will be conducted at participants'homes to minimize travel burden. Local enumerators, trained by the research team, will administer the surveys and assessments. The training will cover the administration of assessment tools, general interviewing techniques and ethical conduct of research. All measures will be available in English, Kiswahili and Kinyabwisha, depending on the preferred language of the participant. Table 1 provides a summary of the primary and secondary outcomes, including their validation status. The data collection forms are available on request. To ensure data quality, the core research team in Uppsala will conduct daily checks on the number of records uploaded and the completeness of these records.

### Plans to promote participant retention and complete follow-up {18b}

To maximize participant retention and ensure complete follow-up, several strategies will be employed. Participants will receive compensation of approximately 3 USD in local currency for each of the three survey rounds. Refreshments will be provided during training and group activities for those in the intervention arms. To reduce the burden of participation and minimize travel, 3-month follow-up surveys will be conducted in participants’ homes. Furthermore, we will maintain regular communication with participants and community leaders to foster a sense of connection and address any concerns. We have also gathered direct and close contact information and are in touch with village leaders, ensuring that we can effectively track down participants at the 12-month endpoint. Finally, enumerators will be trained to build rapport with participants and emphasize the importance of their continued involvement in the study.

### Data management {19}

Data will be entered directly onto password-protected tablets assigned to each enumerator. Data uploaded through KoboCollect will be encrypted and captured securely on the humanitarian server hosted by KoboToolBox. Enrolled participants will be assigned a unique participant ID that will be used to identify them across all three time points, facilitating linkage of data while maintaining anonymity in the dataset. The principal researcher in Uganda will be responsible for overseeing data management in the field. Data will be cleaned and checked for errors. Range checks will be performed to identify outliers.

### Confidentiality {27}

All data will be stored securely and confidentially. Participants’ identifying information will be kept separate from the survey data. Access to data will be restricted to authorized personnel only. Participants will be fully informed of their rights concerning data privacy and the use of their information, in accordance with GDPR principles.

### Plans for collection, laboratory evaluation and storage of biological specimens for genetic or molecular analysis in this trial/future use {33}

Not applicable. No biological specimens will be collected, and no genetic or molecular analyses will be conducted.

## Statistical methods

### Statistical methods for primary and secondary outcomes {20a}

For the primary analysis, the results will be based on an intention-to-treat (ITT) approach, using the initial randomization of the intervention arms. Secondary analyses will employ a per-protocol approach, including only participants who completed the allocated intervention as planned. Analyses will focus on the primary outcome of food insecurity and the secondary outcomes of household dietary diversity, child malnutrition and maternal psychological distress at the 12-month endpoint. Maternal psychological distress measured at 3 months will serve as a manipulation check to verify that SH + was effective. Analyses will be conducted at the individual level, comparing the change from baseline to follow-up between arms, adjusting for clustering and baseline score.

The preliminary analysis will compare participant sociodemographic characteristics and outcome variables across the three intervention arms at baseline. Hierarchical models will be used to examine differential effects of intervention arms on outcomes. Assuming a parametric approach, we will employ models with random effects to account for clustering at the village level and repeated measures within participants. The fixed effects included in the models will be (1) intervention, represented by two indicator variables; (2) time, measured at baseline, 3-month follow-up and 12-month follow-up; and (3) the interaction between intervention and time. Fixed effects parameters will be tested with the Wald test (*t* test, *p* < 0.05, two-sided) and 95% confidence intervals without adjustment for multiple comparisons for the global test of treatment effects. A significant interaction of intervention and time suggests differential intervention effects and will be followed by pairwise comparisons to test the primary hypotheses: the EUC group vs. the HGI group, and the HGI group vs. the SH + HGI group. Participants’ demographic characteristics, baseline levels of primary and secondary outcomes and our village stratification variable (accounting for the settlement patterns of recent arrivals) will be included as covariates in the analyses.

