#### Enhanced usual care

All enrolled participants will receive EUC, which consists of a single 15-min psychoeducation session with a trained assistant overseen by a qualified mental health professional, delivered before the start of the other interventions. The session is guided by a predetermined script, addressing the issue of overthinking and offering self-management techniques [46]. Participants will also receive information on utilizing existing mental health services and UNHCR partner organizations that provide psycho-social support within the refugee settlement, as well as information about a network of trained community health workers offering basic psychosocial support.

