#### Home gardening intervention

The HGI is designed to promote climate-smart farming techniques, empowering participants to achieve greater self-sufficiency [24]. The intervention provides training on growing nutrient-dense crops on small plots near participants’ homes, emphasizing year-round cultivation, sustainable farming practices and knowledge transfer [47]. The HGI utilizes a four-pronged strategy: (1) supplying tools, seeds, and other essential materials; (2) offering education on home-based sustainable agricultural practices; (3) providing lessons on nutrition and cooking; and (4) teaching sustainable harvesting and market strategies.

The program starts with a 3-day training of trainers (ToT) for 20 model farmers and the monitoring team, led by senior trainers specializing in sustainable agriculture. Village-level training of the participants includes three in-person sessions with senior trainers at model farmers’ plots, each lasting approximately 6 h, with at least 2 h devoted to hands-on practice. The timing of these sessions will be staggered across the three strata. Thereafter, trained model farmers located in each village will provide continual support to participants throughout the intervention period. Each participant will receive regular in-person visits at their home garden from a model farmer or assistant monitor.

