#### Self-help plus

Self-Help Plus (SH +) is a transdiagnostic WHO intervention package based on Acceptance and Commitment Therapy that provides tools for guided self-help, empowering participants to manage stress and cope with adversity independently [39, 48]. SH + is delivered by trained, non-specialist facilitators to groups of up to 30 people via a 5-session guided self-help course. The intervention is designed to be adaptable to different cultures and languages. For this study, all SH + materials were professionally translated into Kiswahili following WHO guidelines. The Kiswahili version will be made openly available on the WHO website. The intervention teaches stress management skills through pre-recorded audio files, complemented by guided discussions among participants, using an illustrated guidebook and short audio files to practice skills outside of sessions. Two facilitators support each session by providing additional explanations, demonstrating skills alongside the audio and guiding discussions based on a course manual. The facilitators will receive specialized training from experienced mental health specialists from vivo international Uganda. These specialists will also provide ongoing supervision and support to the facilitators throughout the intervention period. This includes reviewing session plans, observing sessions in-person, providing feedback and guidance to facilitators and addressing any challenges that arise during implementation. This ensures fidelity to the SH + model and supports facilitators in delivering the intervention effectively.

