### Methods in analysis to handle protocol non-adherence and any statistical methods to handle missing data {20c}

The primary analysis will be based on an intention-to-treat (ITT) approach. A per-protocol analysis will be conducted as a secondary analysis. Missing data will be handled using imputation estimation methods (maximum likelihood, K-Nearest Neighbors) estimation if missing at random. We will utilize a conservative last-observation-carried-forward (LOCF) approach for missing follow-up data among completers.

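### The completers-only per-protocol analysis filters the three arms unequally, so its HGI vs EUC contrast can be biased, probably in favour of HGI; the primary ITT result is not affected

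*Protocol article*

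**What the plan says.** All references are to the protocol article.

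- **Primary set** (Statistical methods {20a}): "the results will be based on an intention-to-treat (ITT) approach, using the initial randomization of the intervention arms".
- **Per-protocol set** (same section): secondary analyses are per-protocol, "including only participants who completed the allocated intervention as planned". Section {20c} repeats it: "A per-protocol analysis will be conducted as a secondary analysis".
- **EUC** (Enhanced usual care): "All enrolled participants will receive EUC, which consists of a single 15-min psychoeducation session". By Participant timeline {13}, every arm gets this session before anything else.
- **HGI** (Home gardening intervention): three village training sessions, "each lasting approximately 6 h, with at least 2 h devoted to hands-on practice", followed by regular visits to each mother's garden.
- **SH + HGI** (Self-help plus; Intervention description {11a}): SH+ is delivered "to groups of up to 30 people via a 5-session guided self-help course" and comes before the whole of HGI.
- **Leaving an intervention** (section {11b}): mothers may stop at any time without giving a reason.
- **Model** (section {20a}): covariates are demographics, baseline levels of the primary and secondary outcomes, and stratum. Pairwise comparisons follow a significant intervention-by-time interaction.

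**The concern.** A per-protocol contrast is fair only if the mothers kept in one arm are comparable with those kept in the other. Here the same wording sets very different hurdles. Nearly every EUC mother can be expected to pass, while HGI mothers must sustain about 18 h of training (3 x 6 h) plus visits.

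The article's own rationale suggests that those who pass will differ. The Background ties successful adaptation to psychological capacity, and the K6 entry under Secondary outcomes describes distress as an obstacle to taking up what HGI promotes. If completers would have had lower FIES scores anyway, the HGI completers would look better than EUC with no treatment effect. A per-protocol estimate larger than the ITT estimate could then be misread as a dose effect. This is the only non-adherence analysis the article names, and it covers the primary outcome.

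**Working it through.** **1. The plan's own figure.** Inputs from Sample size {14} and the Abstract: ICC 0.01, variance explained 0.50 (individual) and 0.20 (cluster), 30 villages allocated 1:1:1, 30 dyads per village, 20% attrition, 95% power, two-sided 5%. A pairwise contrast has J = 20 villages and n = 30 x 0.8 = 24 mothers analysed per village.

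SE = sqrt[0.01 x 0.80/(0.25 x 20) + 0.99 x 0.50/(0.25 x 20 x 24)] = sqrt(0.0016 + 0.004125) = 0.0757.

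Minimum detectable difference = (t0.975 + t0.95) x SE = 0.290 with 18 df, or 0.291 with 17 df. The stated 0.291 SD reproduces, and this point does not touch it.

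**2. What completion requires**

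| Arm | Sessions beyond the common EUC session | Total sessions |
|---|---|---|
| EUC | 0 | 1 |
| HGI | 3, plus visits | 4, plus visits |
| SH + HGI | 5 + 3 = 8, plus visits | 9, plus visits |

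**3. Size under no true effect, HGI vs EUC.** Assumptions, none of them from the article: EUC completion 100%; HGI completion p of 60-80%; completers better than non-completers by g = 0.1-0.4 SD *after* the planned covariate adjustment.

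Bias = (1 - p) x g.

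SE = sqrt[2 x 0.008/10 + 0.495 x (1/240 + 1/(240p))], where 0.008 = 0.01 x 0.80, 0.495 = 0.99 x 0.50 and 240 = 10 x 24. The rejection rate comes from a non-central t with 17 df.

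| p | g | Bias (SD) | SE | Share of 0.291 | False positives, free-standing 5% test |
|---|---|---|---|---|---|
| 80% | 0.1 | 0.02 | 0.079 | 7% | 5.7% |
| 80% | 0.2 | 0.04 | 0.079 | 14% | 7.7% |
| 70% | 0.3 | 0.09 | 0.081 | 31% | 18% |
| 60% | 0.1 | 0.04 | 0.084 | 14% | 7.3% |
| 60% | 0.4 | 0.16 | 0.084 | 55% | 43% |

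**4. With the interaction test as a gate.** Village means were simulated with the same variances, three arms of 10 villages, SH + HGI completion set equal to HGI, and a global 5% test required first. The HGI vs EUC false-positive rate becomes about 4% (80%, 0.2 SD), 11% (70%, 0.3 SD) and 33-34% (60%, 0.4 SD).

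**5. Check by a different route.** Let completion depend on a latent trait correlated r with the 12-month residual. Completers' residual mean then shifts by r x phi(c)/p, where c is the normal cut-off giving completion p, and sqrt(0.5) converts this to total SD. Assume EUC completion of 98%. In simulated trials (5,000 replicates, no gate):

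| Completion | r | Bias (SD) | Completers-only rejects |
|---|---|---|---|
| 98% vs 80% | 0.2 | 0.04 | 8.0% |
| 98% vs 70% | 0.1 | 0.03 | 6.3% |
| 98% vs 70% | 0.3 | 0.09 | 18.9% |
| 98% vs 60% | 0.3 | 0.13 | 29.6% |
| 98% vs 98%, and 70% vs 70% | 0.3 | about 0 | 5.1-5.2% |

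ITT in the same trials rejects in 4.5-5.2%. The inflation disappears when completion is equal, so unequal completion combined with selection is its source.

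**6. H2.** For HGI vs SH + HGI at an assumed 70% vs 50% completion, the bias is 0.04 SD (7.2% false positives) at r = 0.2 and 0.06 SD (10.3%) at r = 0.3, without the gate.

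**The case against.** - **It is only secondary.** This stands. H1 and H2 are tested in the ITT model, and nothing lets the per-protocol result override it. A reader might infer that the trial's main conclusion is at risk; the article does not support that.
- **The covariates deal with it.** This stands in part. Distress is the one selection route the article itself points to, and baseline K6 and FIES are in the model. Eligibility at K6 of five or more also narrows the range of distress. Motivation, physical health and labour capacity remain unadjusted, and a residual gap of 0.1 SD, with only 6-7% false positives, is as compatible with the article as a larger one.
- **The gate is part of the plan.** This stands. At the mild setting it removes the inflation altogether, so the free-standing 43% must not be read as what the plan would deliver.
- **The direction is not certain.** This stands. Tools, seeds and refreshments may draw the neediest mothers, which would reverse the sign. A reader might infer a certain bias towards the more demanding arm, but the article gives neither completion rates nor any link between completion and outcome.
- **The rule applies to every arm.** This is correct. It does not drop mothers from the active arms only; the expected numbers dropped differ.
- **The analysis plan may define completion.** It may, and a missing threshold is no fault in an article. But the article does fix a completers-only set, and no threshold makes one 15-minute session comparable with three or eight further sessions.

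**Conclusion.** The point holds as a limited one. The stated per-protocol rule filters the arms unequally, so its HGI vs EUC contrast can be biased, probably in favour of HGI. Under assumed HGI completion of 60-80% and a residual completer gap of 0.1-0.4 SD, the bias is 0.02-0.16 SD. False positives are about 6-43% for a free-standing test. With the interaction gate they are about 4%, 11% and 34% at the three settings shown. If completion is near 100% in every arm, or unrelated to outcome given the covariates, the bias is negligible.

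A reader might extend the contrast of selected with nearly unselected mothers to H2. That does not fit: both arms are selected there, and a smaller bias arises only if completion differs between them. The ITT analysis and the sample size are unaffected. This is a cheap improvement, not a defect in the primary analysis.

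**What to change.** Make a complier-average effect the main non-adherence analysis, with the randomised arm as instrument, all randomised mothers kept, and the same covariates and clustering as the ITT model.

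- **H1 (HGI vs EUC):** exposure is any receipt of HGI, whether training, materials or visits. Training attendance alone is too narrow, because materials and home visits may reach mothers who attend no session, which would breach the exclusion assumption. If nearly every HGI mother receives something, the estimate will lie close to ITT.
- **H2 (SH + HGI vs HGI):** exposure is any SH+ session attended.
- **Completers-only comparison:** if kept, label it descriptive and do not offer it as evidence for H1 or H2.

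Cost: a wording change and one extra model, settled before 12-month outcomes are seen; attendance and receipt recorded per mother (the per-protocol set already needs completion status); wider intervals; and an explicit statement of the assumption that allocation has no effect on mothers who receive none of the defined exposure.

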#### Primary outcome

The primary outcome of this study is food insecurity, which will be measured using the Food Insecurity Experience Scale (FIES) [50] at 12 months post-intervention. The FIES consists of eight questions addressing self-reported food-related behaviors and experiences associated with increasing difficulties in accessing food due to resource constraints. The FIES is unique as it is the most widely used method for evaluating food security at the household or individual level that allows for global comparability [50, 51]. The analysis metric will be the change in the FIES score from baseline to the 12-month follow-up, and the method of aggregation will be the median FIES raw score for each group.

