### Sample size {14}

The sample size calculation was conducted using *PowerUp* [60]*!* and was based on the primary outcome of food insecurity. A total sample size of 900 mother–child dyads (300 per arm) is required to detect a between-arm difference in the primary outcome of 0.291 standard deviations with 95% power and an alpha of 0.05. This calculation assumes an intra-cluster correlation coefficient (ICC) of 0.01, based on previous studies in similar settings [61, 62], and accounts for 50% of the variance being explained by individual-level covariates and 20% by cluster-level characteristics. The calculation also assumes a conservative 20% attrition rate at the 12-month follow-up.

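### If the within-participant random effect is a plain random intercept, the standard error of the 12-month change is averaged over all three visit pairs, and the 5% level of H1 and H2 is not guaranteed

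*Protocol article*

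**What the plan says.** All of this stands in the protocol article; section numbers are in braces.

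- **Model ({20a}).** If outcomes are analysed parametrically, "we will employ models with random effects to account for clustering at the village level and repeated measures within participants". Arm, time and their interaction enter as fixed terms, with "time, measured at baseline, 3-month follow-up and 12-month follow-up".
- **Test ({20a}).** "Fixed effects parameters will be tested with the Wald test", two-sided at 0.05.
- **Order of testing ({20a}).** "A significant interaction of intervention and time suggests differential intervention effects and will be followed by pairwise comparisons to test the primary hypotheses". The pairs are "the EUC group vs. the HGI group, and the HGI group vs. the SH + HGI group".
- **Baseline ({20a}).** Baseline is one of the time points in the model, and baseline levels of the primary and secondary outcomes are also listed as covariates.
- **Primary metric (Primary outcome).** "The analysis metric will be the change in the FIES score from baseline to the 12-month follow-up".
- **Setting of visits ({18a}).** "Baseline and 12-month follow-up assessments will be conducted in person at a central location", whereas the 3-month visit takes place at home.

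The text does not say how many participant-level random effects there are. It gives no correlations between visits and no visit-specific standard deviations.

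**The concern.** With three visits, a single random intercept per participant forces one variance for all visits and one correlation for all pairs. The fitted variance of any change score is then the average over the three pairs: baseline to 3 months, baseline to 12 months, and 3 to 12 months. H1 and H2 use only the baseline-to-12-month pair.

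The trial's own schedule gives two reasons why that pair may differ from the average:

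- It spans the longest interval. If correlation fades with time, its change score is more variable than average and the model's standard error is too small.
- Its two visits share a setting that the 3-month visit does not. If the home visit is the odd one out, the pair is more alike than average and the standard error is too large.

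At stake are the p-values and 95% confidence intervals of both primary hypotheses. A larger sample does not cure this, because the error is a ratio of standard errors.

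**Working it through.** **The plan's own figure.** Sample size {14} gives a detectable difference of 0.291 SD. Inputs for one pairwise comparison: 20 villages, half per arm, 24 mothers per village (30 less 20%), ICC 0.01, and 50% and 20% of variance explained at individual and cluster level. With 17 degrees of freedom (one cluster covariate):

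- variance = 0.01 × 0.8 / (0.25 × 20) + 0.99 × 0.5 / (0.25 × 20 × 24) = 0.0016 + 0.004125 = 0.005725, square root 0.0757
- multiplier = 2.110 + 1.740 = 3.849
- detectable difference = 3.849 × 0.0757 = 0.291

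The stated figure reproduces. It treats a single endpoint and uses no visit correlation, so it neither supports nor answers this point.

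**Standard error under a random intercept.** Assume complete data, a saturated arm-by-time mean and unit variance at each visit. Write r for a correlation and b12 for the baseline–12-month pair.

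- Model variance of the 12-month change: 2(1 − mean r over the three pairs)
- True variance: 2(1 − r_b12)
- Ratio of true to model SE: √[(1 − r_b12) / (1 − mean r)]
- Type I error of a nominal two-sided 5% test: 2Φ(−1.96 / ratio)

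The correlations below are assumptions, in the order baseline–3, baseline–12, 3–12:

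| Correlations | Mean r | Ratio | Model SE | Type I error |
|---|---|---|---|---|
| .50, .45, .55 | .500 | √(.55/.500) = 1.049 | 5% too small | 6.2% |
| .50, .35, .50 | .450 | √(.65/.550) = 1.087 | 8% too small | 7.1% |
| .60, .40, .60 | .533 | √(.60/.467) = 1.134 | 12% too small | 8.4% |
| .35, .50, .40 | .417 | √(.50/.583) = 0.926 | 8% too large | 3.4% |
| .30, .40, .50 | .400 | √(.60/.600) = 1.000 | correct | 5.0% |

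The model SE is 1/ratio of the true one: 0.95, 0.92, 0.88, 1.08 and 1.00. The last row shows that the correlations can be unequal and the level still be exact.

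Simulation of the first four rows (6,000 trials, 10 villages per arm, 24 mothers each, constant village effect with ICC 0.01) gave 6.5%, 7.3%, 9.0% and 3.2% with a random intercept. An unstructured covariance gave 5.2%, 5.0%, 5.3% and 4.8%.

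**Effect of the interaction test.** Simulation with 300 mothers per arm, complete data and a random intercept (4,000 runs), counting a rejection only after a significant interaction. The second column has no effect in any arm. The third has both active arms better than control by 0.4 SD at both follow-ups, so that only H2 is null:

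| Correlations (b–3, b–12, 3–12) | No effect: H1 / H2 | H2 null only |
|---|---|---|
| .60, .40, .50 | 2.3% / 2.2% | 7.6% |
| .70, .35, .50 | 3.4% / 3.0% | 9.1% |
| .40, .60, .40 | 0.6% / 0.6% | 2.3% |

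When home gardening works, the interaction is almost always significant and the preliminary test gives H2 no protection.

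**The case against.** **The covariance is not stated, and such detail is often left to an analysis plan.** This stands in part. The plural in {20a} does not say that there is one effect per participant, and it is satisfied by one effect for village and one for participant. But the section does fix a mechanism, three visits and model-based Wald tests, and the plain reading of these has the consequence shown. A reader might infer that the protocol commits to a single random intercept. It does not, so the point is conditional.

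**The direction is unknown.** This stands. The two reasons for unequal correlations pull in opposite directions and can cancel. A reader might infer that the error rate of both hypotheses is above 5%. The documents give no correlations, so they do not support that.

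**The interaction test protects the pairwise tests.** It does when no arm has an effect. It does not protect H2 when home gardening works and Self-Help Plus adds nothing, which is a central scenario for this trial.

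**Baseline is a covariate, so the problem disappears.** It does not while baseline is also a response. The covariate is constant within a mother and cancels from her change. In simulated data at (.60, .40, .60), the SE of the 12-month interaction was 0.0886 with and without it, against 0.0962 from the change scores. If only the two follow-ups were responses, a single visit pair would remain and the three-pair averaging would go. However, {20a} lists baseline as a level of time.

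**Conclusion.** The point holds conditionally. If the participant term is a random intercept, the 5% level of H1 and H2 holds only where the variance of the baseline-to-12-month change happens to equal the three-pair average, and nothing in the protocol supports that equality. Across the four assumed patterns with unequal change variances, the type I error of a 12-month contrast taken on its own is about 3% to 8%, with a model SE between 12% too small and 8% too large. Allowing for the interaction test, inflation matters mainly for H2 when home gardening is effective.

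These figures assume complete data, equal variances across visits and a village effect that is constant over time. Child height-for-age is unaffected, because with two visits there is only one pair to estimate from.

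A reader might also infer that an unstructured visit covariance secures the 5% level outright. That was shown only for a constant village effect. Village-by-visit variance is a separate issue: at an assumed 1% of total variance and equal correlations of .5, the error was about 12% with a village random intercept alone, and an unstructured participant covariance did not repair it.

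**What to change.** In Statistical methods {20a}, for FIES, HDDS and K6, replace the participant random effect by an unstructured covariance over visits within participant (own variance per visit, own correlation per pair), and keep the village-level random term or terms.

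State how the outcome's own baseline enters, and use it once:

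- either keep all three visits as responses with a 3×3 matrix and drop the own-baseline covariate;
- or model only the 3- and 12-month values with a 2×2 matrix, with baseline by visit as a covariate.

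It cannot be both. With an unstructured matrix, as the baseline coefficient approaches 1 the residual at the baseline visit goes to zero. Its variance can shrink with it, and the likelihood rises without bound. Height-for-age needs no change on this point.

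**Cost.** A sentence or two of text and a few variance parameters: a 3×3 matrix has 6 against 2 for a random intercept, so four more; a 2×2 matrix has 3, so one more. Both are easily estimated from about 900 mothers, even with the planned 20% attrition. No data or participants are lost. Baseline collection was still under way when the manuscript was submitted (Trial status), so the choice can be fixed before 12-month outcomes are analysed. Village-by-visit variance needs its own decision.

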**Methods:**

This study employs a three-arm, parallel-group, cluster-randomized controlled trial (cRCT) in the Nakivale refugee settlement, Uganda. Thirty villages within the settlement will be randomized in a 1:1:1 allocation ratio to one of three conditions: Enhanced Usual Care, a Home Gardening Intervention (HGI) or HGI combined with the peer-delivered psychosocial intervention Self-Help Plus (SH + HGI). A total of 900 refugee mothers and their children (aged 3–4 years) will be enrolled, with 30 dyads per village. The primary outcome is food insecurity at 12 months post-intervention, assessed using the Food Insecurity Experience Scale (FIES). Secondary outcomes include dietary diversity, child malnutrition and mothers’ psychological distress. Data will be collected at baseline, 3-month and 12-month follow-ups. Primary analyses will use an intention-to-treat (ITT) approach.

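### Section {20a} describes two conflicting primary analyses, with baseline FIES as both response and covariate in one; the sample size supports only the baseline-adjusted one.

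*Protocol article*

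**What the plan says.** Protocol article, Statistical methods for primary and secondary outcomes {20a}, gives two accounts of the main analysis.

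- The first paragraph describes an individual-level analysis "comparing the change from baseline to follow-up between arms, adjusting for clustering and baseline score". This is an ANCOVA-type comparison.
- The second paragraph describes a model with random effects for village and for repeated measures within participants. Its fixed effects are intervention, "time, measured at baseline, 3-month follow-up and 12-month follow-up; and (3) the interaction between intervention and time". A significant interaction is the gateway to the pairwise tests of the two primary hypotheses. The covariates of this same model include "baseline levels of primary and secondary outcomes and our village stratification variable", and no covariate-by-time terms are mentioned.

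Sample size {14} states that 900 dyads suffice to "detect a between-arm difference in the primary outcome of 0.291 standard deviations with 95% power and an alpha of 0.05". The calculation "accounts for 50% of the variance being explained by individual-level covariates and 20% by cluster-level characteristics".

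**The concern.** If baseline is a level of time, each participant's baseline FIES is a row of the response. If baseline FIES is also a covariate, that row is regressed on itself. The coefficient of interest, arm by 12 months, then measures how the arm difference changes from baseline. That is a difference in change scores, and anything constant over time within a participant drops out of it.

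The sample size takes credit for covariates halving the individual-level variance. That credit belongs to an analysis in which baseline is adjusted for. It does not carry over to the interaction.

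Two things are at stake. First, the stated power may not describe the test that opens the way to the primary hypotheses. Second, with 10 villages per arm, chance baseline differences are plausible, and the two analyses can then give different estimates. Leaving both open allows a choice after the results are known.

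**Working it through.** **Inputs.** From the abstract and Sample size {14}: 30 villages allocated 1:1:1, so J = 20 per pairwise comparison with P = 0.5; 30 dyads per village less 20% attrition, so n = 24; ICC 0.01; R² 0.50 at individual level and 0.20 at cluster level; alpha 0.05, two-sided according to {20a}. The baseline to 12-month FIES correlation, rho, is not given and is shown as a range.

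**Step 1: reproduce the plan's figure.** For a two-level cluster-randomised design,

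v = ICC(1 − R²₂)/[P(1 − P)J] + (1 − ICC)(1 − R²₁)/[P(1 − P)Jn]

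= 0.01 × 0.8/5 + 0.99 × 0.5/120 = 0.0016 + 0.004125 = 0.005725.

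With 17 degrees of freedom (one cluster-level covariate), the detectable effect is (2.110 + 1.740) × √0.005725 = 3.849 × 0.07566 = 0.2913 SD. Noncentral-t power at 0.291 SD is 95.2%. The stated figure is therefore reproduced, and it uses the factor 0.50.

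**Step 2: what the covariates do to the interaction.** Write the response of participant i at time t as arm, time and arm-by-time terms plus βxᵢ, where xᵢ does not vary over time. In the difference between month 12 and baseline, βxᵢ cancels. With complete data the interaction estimate and its standard error do not depend on which such covariates are listed; with dropout this is approximate.

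A simulated data set (20 villages of 24, rho 0.5, village and participant random intercepts) confirms it:

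| Covariates in model | Arm × 12 months | SE | Participant variance |
|---|---|---|---|
| none | −0.2502 | 0.0950 | 0.415 |
| baseline | −0.2502 | 0.0950 | 0.050 |
| baseline + a prognostic covariate | −0.2502 | 0.0950 | 0.037 |

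The covariates absorb participant variance, which the interaction does not use. ANCOVA of the 12-month value on the same data, without a village term, had SE 0.079.

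**Step 3: power of the interaction at 0.291 SD.** The individual variance of a change score is 2(1 − rho) times that of a single measurement, so 2(1 − rho) replaces 0.50. The village part is bracketed. Either it stays at the planned 0.0016, or it is zero because stable village effects cancel in the difference. The last column keeps the planned village part and uses 1 − rho², which is adjustment for baseline alone.

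| rho | 2(1 − rho) | Interaction, planned village term | Interaction, village effects cancel | 1 − rho² | Baseline-only ANCOVA |
|---|---|---|---|---|---|
| 0.3 | 1.40 | 67% | 72% | 0.91 | 82% |
| 0.5 | 1.00 | 79% | 86% | 0.75 | 87% |
| 0.707 | 0.586 | 93% | 98% | 0.50 | 95% |

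Example at rho 0.5: v = 0.0016 + 0.99 × 1.00/120 = 0.00985, giving a detectable effect of 3.849 × √0.00985 = 0.382 SD at 95% power.

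**Step 4: break-even.** With the planned village term, 2(1 − rho) = 0.50 gives rho = 0.75. If village effects cancel, 95% power is reached at rho of about 0.65.

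None of these figures includes any further loss from requiring a significant global interaction before the pairwise tests.

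**The case against.** A reader might infer that the trial does not have its 95% power. The documents do not support that, for four reasons.

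- Differencing removes stable differences between participants and between villages, so the interaction reaches 95% if rho is high enough. No rho is given, so the power claim is unsupported for this test, not shown to be false.
- The first paragraph of {20a} states a baseline-adjusted analysis, for which 0.291 SD at 95% follows from the plan's own inputs.
- Setting the interaction at rho 0.3 against a fixed R² of 0.50 is not like for like. Baseline would then explain 9% of the variance, and other covariates would have to supply the remaining 41 points. If they did not, the baseline-adjusted analysis would also miss 95% (82%). If baseline supplied the whole 50%, the interaction would lose only about 2 points with the planned village term, and nothing if village effects cancel.
- The scale of the follow-on pairwise comparisons is not stated. Read as arm differences at month 12, they would benefit from the baseline covariate. If the correlation is equal between all time points, the pooled slope is (1 + 2rho)/3. At rho 0.5 the variance factor is then 0.78, against 0.75 for ANCOVA and 1.00 for a change score.

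All four stand and limit the claim. It would also be wrong to call the baseline data wasted, since a change contrast uses them. Under randomisation that contrast is unbiased. None of this removes the double use of baseline or the conflict within {20a}. The interaction still gates the primary tests whatever scale the pairwise comparisons use, and the slope that it imposes on the month-12 comparison is pulled towards 1 by the baseline rows.

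**Conclusion.** The point holds as an inconsistency with a conditional effect on power. Section {20a} describes two different primary analyses. The one with its fixed effects and test sequence written out uses baseline FIES as both response and covariate, and its interaction gains no precision from covariates entered as time-constant main effects. The variance credit in {14} therefore supports only the baseline-adjusted analysis.

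For the interaction, 95% power at 0.291 SD requires rho of at least about 0.75, or about 0.65 if stable village effects cancel. Below that, over assumed values from 0.3 to 0.6, power is roughly 67–86% (72–92% if village effects cancel). These figures rest on the plan's own ICC, cluster size and attrition, on equal variance at baseline and month 12, and on covariates entering without time interactions, which is how {20a} reads. The matter is one of efficiency and of fixing a single analysis in advance; no bias is alleged.

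**What to change.** In {20a}, choose one role for baseline and delete the wording that gives it both.

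- **Preferred:** model FIES at 3 and 12 months with arm, time, arm × time, baseline FIES × time, stratum and the listed covariates, with random effects for village and participant. Name the month-12 arm differences (HGI vs EUC, SH+HGI vs HGI) as the primary contrasts. This matches the calculation in {14}.
- **Alternative:** keep baseline as a response only, with one common baseline mean across arms, and the same month-12 contrasts.

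If the interaction test is kept, restate the power in {14} for a change-score contrast and give the assumed rho and its basis.

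The cost is a reworded paragraph, with no new data. The article's Trial status section reports baseline collection still under way at submission, so the change could be made before any 12-month outcome exists.
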